## Abstract

**Introduction::**

Although single-incision laparoscopic appendectomy (SILA) was introduced decades ago, it is still considered a difficult technique to perform compared to conventional laparoscopic appendectomy (CLA). In addition, controversy about the benefits of SILA compared to CLA abound and no definite criteria for choosing SILA over CLA in patients with appendicitis currently exist. Therefore, we have planned a multi-center randomized controlled trial to compare SILA with CLA in terms of cosmetic satisfaction and pain reduction.

**Methods and analysis::**

Patients diagnosed with appendicitis at the participating centers will be recruited and allocated into either a CLA or an SILA groups using a 1:1 randomization. Patients in the CLA group will receive a conventional 3-port laparoscopic appendectomy and patients in the SILA group will receive a laparoscopic appendectomy using a single-incision at the umbilicus. The primary trial endpoint is cosmetic satisfaction assessed using the Patients and Observer Scar Assessment Scale (POSAS) administered 6 weeks post-surgery. Secondary trial endpoints include cosmetic satisfaction assessed via the Body Image Questionnaire, pain levels assessed via the Visual Analog Scale and International Pain Outcomes questionnaire, and the presence of postoperative complications. The target sample size of this superiority trial is 120 patients, as this will provide 80% power at the 2.5% level of significance to detect a 3-point difference in POSAS.

**Discussion::**

The results of this planned multi-center randomized controlled trial will provide substantive evidence to help surgeons choose when to use SILA over CLA in patients with appendicitis.

**Ethics and dissemination::**

This trial was approved by the institutional review board at Daegu joint on February 27, 2020 (No: 19-12-001-001) and registered with the clinical research information service (CRIS) (KCT0005048). The results of the study will be published and presented at appropriate conferences.

**Highlights:**

## Background

Acute appendicitis is one of the most common causes of emergency gastrointestinal surgery worldwide. Even though controversy regarding the medical management of acute appendicitis using antibiotics exists, appendectomy is currently considered the gold standard treatment.

Open appendectomy rather than laparoscopic appendectomy was performed universally until the 1990s, even though Kurt Semm, a German gynecologist, first introduced laparoscopic appendectomy firstly in 1983 [1]. Currently, most appendectomies are laparoscopic because of the advantages including early recovery, less pain, and improved cosmetic satisfaction compared with open appendectomy [2].

A conventional laparoscopic appendectomy (CLA) usually requires insertion of three port trocars with two working ports and one camera port. Additionally, single-incision laparoscopic appendectomy (SILA) has become popular since it was first introduced in 1992 [3]. Recent meta-analysis reported that SILA is a safe and feasible procedure compare to CLA, though SILA is a considered more technically demanding than CLA [4,5,6].

Theoretically, SILA would be expected to produce less pain, encourage faster recovery, and result in better cosmetic satisfaction than CLA. However, several previous reports comparing SILA and CLA have yielded conflicting results and only a few studies have reported that SILA is superior to CLA with respect to pain and/or cosmesis [7,8,9,10,11]. One randomized control trial (RCT) failed to show the superiority of SILA over CLA with respect to pain and cosmesis [12]. Furthermore, a recent meta-analysis reported no differences in the pain and cosmesis scores between SILA and CLA [5,13]. Several studies, rather, have even reported that postoperative pain is more severe after SILA than after CLA [14,15].

Previous RCTs compared between SILA and CLA used simple visual analog score (VAS) for the assessment of both pain and cosmetic satisfaction. Results originated from this type of assessment have limitations with regard to their objectiveness.

There are several patient-reported outcomes measures (PROMs) used for assessing the pain and cosmetic satisfaction after surgery including the International Pain Outcome (IPO) Questionnaire [16], the Patient and Observer Scar Assessment Scale (POSAS) [17], and the Body Image Questionnaire (BIQ) [18]. However, there is a paucity of literature reporting outcomes comparing SILA and CLA using these tools.

Therefore, our trial aims to investigate the clinical benefits of SILA over CLA using these more objective PROMs for pain and cosmetic satisfaction.

## Methods

### Study design

This study is a multi-center, prospective, open-label, randomized trial. Patients diagnosed with acute appendicitis at participating centers will be screened for study enrollment. Enrolled participants will be randomly allocated to either the SILA group or the CLA group. This study follows the recommendations of the SPIRIT (Standard Protocol Items: Recommendations for Interventional Trials) guidelines. The study flowchart is shown in ***Figure 1***.

**Figure 1 F1:**
[figure not shown]
Study flow chart. CLA, Conventional Laparoscopic appendectomy; ITT, intention-to-treat; PP, per-protocol; SILA, Single-Incision Laparoscopic Appendectomy.

### Inclusion criteria

Patients 19–75 years of age diagnosed with acute appendicitis who will receive a laparoscopic appendectomy will be recruited. Diagnosis of acute appendicitis is confirmed by abdominopelvic CT or ultrasonography performed on patients with clinically suspected appendicitis, and is defined by appendiceal diameter exceeding 6 mm with thickened and enhancing wall, and periappendiceal edema or fluid collection.

### Exclusion criteria

Patients who have one or more of the following will be excluded from this study: (1) patients with a suspected abscess or appendiceal perforation; (2) patients with symptoms of pan-peritonitis symptom; (3) patients with a history of major abdominal surgery; (4) patients who have an inability to express themselves due to conditions such as dementia or intellectual disability; (5) patients with chronic pain who need to take analgesics; (6) patients with severe medical disease such as pulmonary, cardiovascular, hepatic, or renal insufficiency; (7) Pregnancy; and (8) patients unable to provide consent.

### Interventions

#### SILA (Figure 2A)

A single 2cm incision will be made at the umbilical area and a custom multi-channel single port (Octoport, Dalim company, Co. Ltd., Korea) will be inserted into the incision site. There will be no restrictions placed on the type of laparoscopic instruments used, and all such decisions will be left to the discretion of the surgeon. The mesoappendix and appendiceal artery will be ligated and resected with an energy device or bipolar cauterization. The appendiceal base will be ligated with a loop tie or clip as per the surgeon’s preference. After the appendectomy, the facia will be closed with an absorbable suture and the skin will be closed using a nylon suture, an absorbable subcuticular suture, or a topical skin adhesive as per the surgeon’s preference.

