#### CLA (Figure 2B)

A standard three-trocar technique will be used with incisions made at the peri-umbilical, left lower quadrant, and supra-pubic sites. All other techniques for the appendectomy will be similar to those used in the SILA procedure.

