### Randomization and sample size calculation

All participants will be randomized to either the SILA group or the CLA group in a 1:1 ratio. The randomization allocation will occur just to surgery using a computerized randomization system.

The target sample size will be 120 participants, as this will provide 80% power at the 2.5% (two-sided) level of significance to detect a three-point difference in the POSAS score between the SILA group and the CLA group at 6 weeks after surgery. Our target sample size allows for 10% attrition.

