### Endpoints

The primary trial endpoint is cosmetic satisfaction at 6 weeks after surgery as measured by POSAS. The secondary endpoints are cosmetic satisfaction assessed via BIQ, pain assessed via the IPO questionnaire and VAS, and the presence of general postoperative complications.

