#### Perioperative findings

Intraoperative findings including operative time, estimated blood loss, incision length, intraperitoneal findings, method of appendiceal base ligation, additional port insertion, conversion to open appendectomy, and skin suture technique will be recorded. Postoperative analgesics use, hospital stay, and morbidities within 30 days after surgery will be also collected.

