This study has some limitations even though it was designed as a prospective multi-center RCT. First, there are no Korean validated versions of the PROMs which will be used. However, investigators discussed the bases of clinical similarity and significance of the original version and translated the PROMs into Korean. In addition, all PROMS will be administered under the guidance of investigators or trained clinical nurses. Second, we will not be specifying which appendiceal base ligation or wound closer method must be used and instead will leave these decisions to the surgeon’s preference. This may act as a source of bias affecting the results. However, all the participating surgeons are colorectal surgery specialists who have performed hundreds of laparoscopic colorectal resections including SILA and CLA techniques. As a result, surgical skill should have a minimal impact on postoperative morbidities between surgeons.

In summary, this study is a prospective multi-center RCT designed to compare SILA and CLA with regard to cosmetic satisfaction and postoperative pain. We believe that the results of this study will clarify the efficacy of SILA for the treatment of acute appendicitis and will be helpful for determining which patients would benefit from SILA instead of CLA.

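### Skin closure acts on the scar that the primary endpoint scores, yet it is left to a surgeon who knows the arm, and nothing stated stops it from differing between arms

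*Protocol article*

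**What the plan says.** All references are to the protocol article.

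- **Endpoint** (Endpoints): "The primary trial endpoint is cosmetic satisfaction at 6 weeks after surgery as measured by POSAS". POSAS is a scar scale.
- **Closure in the SILA arm** (Interventions, SILA): "the skin will be closed using a nylon suture, an absorbable subcuticular suture, or a topical skin adhesive", according to the surgeon's preference.
- **Closure in the CLA arm** (Interventions, CLA): not described separately. "All other techniques for the appendectomy will be similar to those used in the SILA procedure".
- **Knowledge of the arm** (Study design; Randomization and sample size calculation): "This study is a multi-center, prospective, open-label, randomized trial", and "The randomization allocation will occur just to surgery using a computerized randomization system". A word seems to be missing from the second sentence, but allocation clearly comes at about the start of the operation, before the skin is closed.
- **Recording** (Perioperative findings): "conversion to open appendectomy, and skin suture technique will be recorded".
- **Limitations** (Discussion): of leaving base ligation and wound closure open, the authors write "This may act as a source of bias affecting the results". They then point to the experience of the participating surgeons and conclude that "surgical skill should have a minimal impact on postoperative morbidities between surgeons".

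**The concern.** For many endpoints in an appendectomy trial, free choice of skin closure would be harmless. Here closure acts directly on the structure that the primary endpoint scores, and the surgeon knows the arm when choosing it. The arms also differ in the number and site of wounds (one umbilical incision against three sites), so a surgeon could close differently by arm without intending to favour either.

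If that happens, the intention-to-treat comparison of POSAS measures port technique together with the closure that accompanied it, and the trial cannot separate the two. The article sees the risk, but its answer does not meet it. Skill and morbidity are not scar appearance, and similarity between surgeons is not similarity between arms. Equally skilled surgeons can still close differently according to the arm.

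Recording the method lets an imbalance be described. It does not repair one, because closure is chosen after randomisation and adjusting for it can itself introduce bias.

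**Working it through.** **1. The plan's own figure.** The article gives 120 patients, 80% power, 2.5% two-sided, a 3-point difference and 10% attrition. It states no SD, so 120 cannot be reproduced directly, only solved backwards:

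- Evaluable patients: 120 × 0.9 = 108, or 54 per arm.
- Implied SD = 3 / [√(2/54) × (2.241 + 0.842)] = 3 / (0.1925 × 3.083) ≈ 5.06.
- If 2.5% is read as one-sided: 3 / [0.1925 × (1.960 + 0.842)] ≈ 5.56.

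The calculations below assume SD 5.0. The point does not depend on this value.

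**2. Size of a closure bias.** Bias = (difference between arms in the use of a method) × (POSAS difference between methods). Both factors are assumptions, because the article gives neither.

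- 10 percentage points × 1 point = 0.1 point
- 33 percentage points × 1 point = 0.33 point
- 17 percentage points × 3 points = 0.51, about 0.5 point
- 33 percentage points × 3 points = 0.99, about 1.0 point, a third of the 3-point target

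**3. Effect on the test.** SE = 5.0 × √(2/54) = 0.962. Rejection probabilities come from the noncentral t distribution with 106 degrees of freedom and noncentrality bias/SE, with no effect of port technique itself. The Statistical analysis section uses 0.05 and the sample size statement uses 0.025, so both are shown.

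| Bias (points) | Bias/SE | Rejection at 0.05 | Rejection at 0.025 |
|---|---|---|---|
| 0.1 | 0.10 | 5.1% | 2.6% |
| 0.33 | 0.34 | 6.3% | 3.3% |
| 0.5 | 0.52 | 8.1% | 4.5% |
| 1.0 | 1.04 | 17.8% | 11.3% |

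At a bias of 1.0 point, SD 5.06 gives 17.4% and 11.1%, and SD 5.56 gives 15.3% and 9.5%.

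**4. The other direction.** With a true 3-point benefit and a 1-point bias against SILA, the apparent difference is 3 − 1 = 2 points. Noncentrality falls from 3/0.962 = 3.12 to 2/0.962 = 2.08, and power at 0.05 falls from about 87% to about 54%.

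**5. Would a covariate cure it?** A closure plan entered before allocation is balanced between arms in expectation. Adjusting for it therefore cannot remove a difference created afterwards. A simulation confirms this (54 per arm, SD about 5, 3-point closure effect, 33-percentage-point difference from switching after allocation, no port effect): the bias was about 1.0 point both before and after adjustment for planned closure.

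**The case against.** The strongest reply is that closure may not differ by arm at all. Surgeon preference can mean each surgeon's habitual method. If surgeons operate in both arms and keep their habits, 1:1 randomisation balances closure in expectation and there is no bias. The CLA section also carries the same options to the other arm. This stands as far as it goes: the article does not say that closure is picked case by case, and nothing in it shows that preference depends on the arm. But similar techniques are not a rule of equal closure, and nothing stated secures the harmless case.

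Second, intention-to-treat validly estimates each technique as delivered. If closure differs because the incisions differ, one can call that part of the technique. This also stands, and it means that the rejection rates above are errors only for a claim about port technique alone. The article does not say which effect it means.

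Third, the risk is disclosed and the method is recorded. That is true, but the disclosure is followed by an argument about a different outcome.

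A reader might infer more: that the primary result is biased, that it is biased towards SILA, or that the false-positive rate is 18%. The article supports none of these. The 18% rests on an assumed 3-point difference between closure methods, as large as the whole target effect, and a 33-percentage-point imbalance. With a 1-point difference and the same imbalance the figure is 6%. The direction is unknown.

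**Conclusion.** The point holds as a gap in protection, not as a demonstrated bias. A determinant of the primary endpoint is chosen after allocation by someone who knows the arm, the two arms are not bound to the same closure, and the defence in the Discussion does not address the scar or differences between arms.

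The size is unknown. Over the assumed range of 0.1 to 1.0 point, with SD 5.0 and 54 per arm, it runs from negligible (5% rejection at 0.05) to material (18%), and it could equally hide a real benefit of SILA. The change is worth making because it is cheap and has to be in place before allocation; analysis cannot supply it later.

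**What to change.** No closure method needs to be prescribed, and the choice stays with the surgeon.

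1. Have the surgeon enter the planned skin closure in the existing computerised randomisation system before the allocation is shown, to be used in whichever arm is drawn.
2. Allow departures at the surgeon's discretion, with the reason recorded.
3. Tabulate planned and actual closure by arm.
4. Planned closure may serve as a covariate or stratification factor for a small gain in precision. It must not be presented as removing bias from departures after allocation.
5. Revise the limitations paragraph of the Discussion to address the scar endpoint, and state that the result is the effect of each technique as delivered, including any difference in closure.

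The cost is one extra field per patient, one table, a revised paragraph, and a mild constraint on changing closure once the arm is known.

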**Figure 2 F2:**
[figure not shown]
Incision and trocar position of SILA **(A)** and CLA **(B)**.

Additional port insertion or conversion to an open surgery will be possible at the surgeon’s discretion to ensure patient safety.

#### CLA (Figure 2B)

A standard three-trocar technique will be used with incisions made at the peri-umbilical, left lower quadrant, and supra-pubic sites. All other techniques for the appendectomy will be similar to those used in the SILA procedure.

### Randomization and sample size calculation

All participants will be randomized to either the SILA group or the CLA group in a 1:1 ratio. The randomization allocation will occur just to surgery using a computerized randomization system.

The target sample size will be 120 participants, as this will provide 80% power at the 2.5% (two-sided) level of significance to detect a three-point difference in the POSAS score between the SILA group and the CLA group at 6 weeks after surgery. Our target sample size allows for 10% attrition.

### Endpoints

The primary trial endpoint is cosmetic satisfaction at 6 weeks after surgery as measured by POSAS. The secondary endpoints are cosmetic satisfaction assessed via BIQ, pain assessed via the IPO questionnaire and VAS, and the presence of general postoperative complications.

### Data collection and management

All data for this RCT will be collected after obtaining consent from the participants prior to surgery. All data will be recorded on a paper case report form as well as a digital record form. A participating surgeon or trained researching nurse will perform the postoperative interview to collect the necessary PROMs data (***Figure 3***).

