#### PROMs for cosmetic satisfaction

POSAS and BIQ will be obtained 6 weeks after surgery in the outpatient clinic. If any participant is unable to attend the clinic, a telephone interview will be permitted for completion of the survey.

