## Discussion

Laparoscopic abdominal surgery is generally regarded as a minimally invasive surgery with advantages such as less pain, faster recovery and better cosmetic results compared with open surgery. Many types of laparoscopic abdominal surgeries are currently used including single-incision procedure and conventional multi-port procedures [19,20,21]. Single-incision laparoscopic abdominal surgery is still a challenging procedure even among experienced laparoscopic surgeons [22,23]. Nevertheless, Appendectomy is one of abdominal surgery that is well-suited for a single-incision laparoscopic approach.

Surgeons and patients believe that reduced port surgery has advantages in terms of cosmetic satisfaction and pain reduction. This belief is based on the results of previous studies comparing open and laparoscopic surgery. In addition, among laparoscopic surgical techniques, SILA would be expected to outperform CLA with regard to cosmetic satisfaction and pain reduction because of further reductions in invasiveness. However, it has been difficult to prove the superiority of SILA over CLA because patient expectations are raised.

In this context, as mentioned above, there are controversies about the efficacy of SILA with respect to cosmetic satisfaction and pain reduction compare to CLA. However, previous studies including RCTs have used only a simple VAS and/or analgesic usage as indicators for pain reduction [8,10,24,25]. Although Anthony et al. [26] used a pain score that assessed overall pain as well as pain during specific activities (e.g. at rest, coughing for 10 time, after standing for 5 minutes), it was too detailed a score to get via PROM and provided only a subjective profile. Therefore, we decided not to use this pain evaluation scale.

For evaluation of cosmetic satisfaction, most previous studies used a subjective numeric rating from 5 to 100 [12,24,26,27]. The Vancouver Scar Scale and BIQ were used in two RCTs, but these studies were limited by their small sample size [8,10]. POSAS was used for the evaluation of cosmetic satisfaction in one recent study, but this study evaluated cholecystectomy and was not an RCT [28]. Therefore, we think that it is necessary to investigate the detailed differences in cosmetic satisfaction and pain reduction between SILA and CLA for appendectomy using objective scales in a study with an adequate sample size.

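### In an open-label trial with a subjective primary endpoint, the plan lets a participating surgeon collect the patient-reported outcomes and does not exclude the surgeon who operated

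*Protocol article*

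**What the plan says.** Study design gives the masking: "This study is a multi-center, prospective, open-label, randomized trial". Endpoints gives the outcome: "The primary trial endpoint is cosmetic satisfaction at 6 weeks after surgery as measured by POSAS". The secondary endpoints include BIQ, IPO and VAS, which are also patient-reported.

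Data collection and management says who obtains these data: "A participating surgeon or trained researching nurse will perform the postoperative interview to collect the necessary PROMs data". The limitations paragraph of the Discussion adds that "all PROMS will be administered under the guidance of investigators or trained clinical nurses". It offers this as mitigation for the lack of validated Korean versions. For the 6-week instruments, PROMs for cosmetic satisfaction allows a second mode: "If any participant is unable to attend the clinic, a telephone interview will be permitted for completion of the survey".

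On who the surgeons are, the Discussion says that "all the participating surgeons are colorectal surgery specialists who have performed hundreds of laparoscopic colorectal resections including SILA and CLA techniques". On what they expect, it says: "Surgeons and patients believe that reduced port surgery has advantages in terms of cosmetic satisfaction and pain reduction".

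The article does not require the interviewer to be masked or independent of the operation. The committee described under Monitoring checks study process and safety; outcome assessment is not among its stated tasks. The limitations paragraph names translation and surgeon-chosen technique, but not unmasked outcome collection.

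**The concern.** A patient who answers questions about a scar in front of the surgeon who made it may answer differently than on paper or to a neutral person. An interviewer who favours one technique may also present or explain items differently without meaning to. If the shift were the same in both arms it would cancel in the comparison. What matters is a shift that differs by arm. The article gives a reason to expect one, because it says surgeons as a group already believe fewer ports are better.

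Such a shift adds directly to the estimated treatment effect on the primary endpoint. Neither the intention-to-treat nor the per-protocol analysis can remove it. The Background justifies the trial by the limited objectiveness of earlier ratings, and this way of collecting the data works against that aim. The component that comes from the interviewer is also avoidable, since the same sentence already names a trained nurse.

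**Working it through.** **What the text permits.** Open-label, a self-reported primary, a participating surgeon as a permitted interviewer, and surgeons described as believing in one arm are four statements in the article. No passage separates the interviewer from the operator. Interviewing by the operating surgeon is therefore permitted, though not required.

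**How a bias enters.** Let c_S and c_C be the average shifts in the two arms when a surgeon interviews, and p the share of interviews done by surgeons, equal in both arms. Then

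observed difference = true difference + p × (c_S − c_C).

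A shift common to both arms (c_S = c_C) drops out. Only the differential part b = p × (c_S − c_C) matters.

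**Inputs for an illustration.**
- From Randomization and sample size calculation: 120 patients, 1:1, 10% attrition, a 3-point difference, 80% power, two-sided 2.5%. Evaluable per arm: 60 × 0.90 = 54.
- From Statistical analysis: significance at p < 0.05. The two levels differ, so both are shown.
- Assumed: the SD, because the article gives none. The target of 120 can therefore be neither reproduced nor refuted, and the SD is back-solved from it.
- Assumed: the size of b.

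**Back-solved SD.** SD = 3 / [√(2/54) × (z for alpha + z for power)], with √(2/54) = 0.1925.
- Two-sided 0.025: 3 / [0.1925 × (2.241 + 0.842)] = 5.06.
- Two-sided 0.05: 3 / [0.1925 × (1.960 + 0.842)] = 5.56.

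**False-positive rate with no true effect.** SE = SD × 0.1925, which is 0.97 for SD 5.06 and 1.07 for SD 5.56. The two-sided rejection rate is Φ(b/SE − z) + Φ(−b/SE − z).

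Example for b = 1, SD 5.06, z = 1.960: b/SE = 1.027, so Φ(−0.933) + Φ(−2.987) = 0.175 + 0.001 = 0.177 before rounding of the terms.

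| Average differential bias b | p < 0.05, SD 5.06 | p < 0.05, SD 5.56 | p < 0.025, SD 5.06 | p < 0.025, SD 5.56 |
|---|---|---|---|---|
| 0 | 5.0% | 5.0% | 2.5% | 2.5% |
| 0.5 | 8.1% | 7.5% | 4.5% | 4.1% |
| 1.0 | 17.7% | 15.4% | 11.3% | 9.6% |
| 1.5 | 33.8% | 28.8% | 24.2% | 20.0% |

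The noncentral t distribution (106 df) at SD 5.0 gives 17.8% and 11.3% for a 1-point bias, so the normal approximation is adequate.

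**Dilution.** If surgeons do half the interviews and nurses add no bias, a 1-point surgeon effect averages to b = 0.5 × 1 = 0.5. The rate at p < 0.05 is then about 8% (7.5–8.1%), not 15–18%.

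**The case against.** **The wording is milder than it may look.** A reader might infer that surgeons steer the answers. The text says only that the questionnaires are administered with guidance from investigators or nurses, in the context of unvalidated translations. That fits help with item wording, and nothing says answers are suggested. This part of the objection stands.

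**The operating surgeon is not named.** The article says a participating surgeon, and an article may leave clinic rosters to the full protocol. But the article does choose who collects the primary outcome, and it does so without excluding the operator. The point is about that stated choice, so it survives.

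**Scar rating by the operator.** POSAS has an observer part, and a reader might infer that operators will score their own scars. No passage says who scores that part or whether it enters the primary endpoint. The inference is unsupported. The fix covers it only as a precaution.

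**Direction.** A reader might take the remark on raised expectations as evidence of bias toward SILA. It says the reverse: "it has been difficult to prove the superiority of SILA over CLA because patient expectations are raised". Only the separate statement about what surgeons and patients believe points toward SILA, so the direction is an inference.

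**Both arms may be affected equally.** The surgeons are experienced in both techniques, and a wish to please one's surgeon applies to both arms. That part would cancel. The surgeons' stated preference for fewer ports is what could make the shift differ by arm.

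**Patients see their own scars.** Expectation bias remains whoever interviews, and the nurse is not described as masked either. This stands, and it limits what the fix can achieve. It is no reason to keep the interviewer component, which can be avoided.

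**Conclusion.** The point holds as a weakness in a stated design choice and should be corrected. The article permits the operating surgeon to collect the subjective primary and secondary outcomes of an open-label trial, and says that surgeons as a group already favour one arm.

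The size of any resulting bias is unknown. The 15–18% (p < 0.05) and roughly 10–11% (0.025) false-positive rates rest on three assumptions: an SD of about 5.0 to 5.6, an average differential bias of 1 point (a third of the 3-point target), and no true effect. They show sensitivity and do not predict what will happen. They would apply to a differential bias from any source.

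The documents do not show that answers are guided, that operators rate their own scars, or that the net bias must favour SILA.

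**What to change.** Under Data collection and management, state that no surgeon interviews, or scores any observer component for, a patient he or she operated on.

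- Patients complete POSAS (patient part), BIQ, IPO and VAS themselves, or with the trained research nurse already listed. If no nurse is available, a participating surgeon who did not operate on that patient steps in.
- Whoever assists may explain the wording of an item but does not suggest an answer.
- Telephone interviews follow the same rule on who may conduct them.
- The CRF records the interviewer's role and the mode (clinic or telephone).
- The sentence on guidance in the Discussion is reworded to match, and the bias that remains because patients are unmasked is listed as a limitation.

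The sample size and the analysis do not change. The cost is scheduling, mainly for VAS at 6 hours and on the mornings of days 1 and 2. The article does not describe nurse cover at the centers, so the statement that no new staff are needed depends on allowing a non-operating colleague as back-up.
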